##### Personality

The ‘Short Five’ (S5) personality inventory is a 60-item questionnaire constructed for measuring 30 facets of the Five-Factor Model [38]. The personality traits measured are the Big Five: neuroticism, openness, conscientiousness, extroversion, and agreeableness [38]. Each item is rated on a 7-step scale from − 3 to + 3. The inventory comprises 30 question pairs, six pairs, i.e. 12 questions for each trait. Questions are scored in pairs so that the score for the second question is deducted from the score for the first question. Sum scores, ranging from − 36 to 36, are calculated for each trait. S5 provides more detailed information than most of the other scales of similar length, and shows better reliability and convergent validity than even shorter questionnaires [38].

##### Physical performance

The Short Physical Performance Battery (SPPB) combines the results of the gait speed, chair stand and balance tests [20]. It has been used as a predictive tool for possible disability and can aid in the monitoring of function in older people. The scores range from 0 (worst performance) to 12 (best performance). The SPPB has been shown to have predictive validity showing a gradient of risk for mortality, nursing home admission, and disability. Studies show that the SPPB is a reliable and valid instrument [39]. In this sample, physical performance was measured at pre-measurement for all groups, and in addition for the web-based group at four and 10-months.

##### Adherence, user experiences, and usage of technology

The post-measurement includes a user experience questionnaire for the web-based intervention group. The questionnaire developed by the research group assesses usability, acceptance, perceived benefits, and usage of the web intervention. The first five questions are rated on a 10-point scale from 1 to 10: 1 = very unsatisfied, 10 = very satisfied (item 1); 1 = not at all important, 10 = very important (items 2 and 4); 1 = very satisfied, 10 = not at all satisfied (item 3); 1 = has deteriorated, 10 = has improved remarkably (item 5). Item 6 assesses current well-being on a 7-point scale, item 7 time spent weekly in the web program on a 4-pont scale (less than 1 h, between 1 and 2 h, 2–3 h and more than 3 h), and the remaining two questions are open-ended questions. The questionnaire also includes open-ended questions such as *What was it like to participate in this program? What have you learned from this program? Was the program easy to use?* The post-measurement will also include interviews for collecting qualitative data that can provide deeper insights into user experiences and perceived benefits. Objective technology usage data will be extracted from log files generated by the web application.

### Statistical analysis

The sample size for the trial was estimated based on the change in depressive symptoms (the primary outcome) measured by the BDI-II in a previous study [40]. A sample size of 50 elderly family caregivers in each of 1) an Acceptance and commitment therapy –based online psychological intervention group (experimental group), and 2) a standardized institutional caregiver rehabilitation program (active comparison group representing usual care), and 3) an active control group receiving support from a caregiver associations receiving support provided by voluntary caregiver associations was calculated as the minimum required to detect a 5.8 point decrease in BDI-II in 1) the ACT intervention group or 2) the standardized institutional caregiver rehabilitation program vs. no change in 3) the caregiver support group at the 10-month post-measurement to achieve 80% power. The calculations were based on a one-sided General Estimation equation (GEE) model [41] using the pre-measurement, four-month and 10-month post-intervention measurements. We assumed that the post-measurement difference between the 1) intervention or 2) usual care group vs. 3) caregiver support group would be 5.8 points (*SD* = 4.8) lower than at pre-measurement (9.3 points, *SD* = 7.8). Thus, assuming an attrition rate of 20%, a sample size of 123 (41 per group) was expected. Hence the target sample size was 150 participants, with 50 in each group.

Statistical analyses will be conducted using Mplus (version 7) [42] and SPSS IBM version 24. Analyses will be performed on all participants. Baseline differences between the groups will be examined by using t-tests and chi-square -tests. Data will be analyzed using the IBM SPSS statistics version 22.0 or newer and Mplus statistical package 7.1. Analyses will be controlled for possible baseline differences between the groups. Between group differences in the stability of the outcome measures will be examined using multiple-group modeling techniques. Full information maximum likelihood (FIML) estimation on the assumption of data missing at random (MAR) will be used in analyzing incomplete data. When the normality assumption is violated, maximum likelihood with robust standard errors (MLR) will be used. The level of significance will be set at 0.05. Cohen’s *d* will be used to estimate effect sizes, and to reflect the clinical significance of the interventions.

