### Outcome measures

#### Main outcome measure

##### Depression

The Beck Depression Inventory [24] will be used as the main outcome measure. It is commonly used in research and clinical practice to measure the presence and severity of depression. It contains 21 questions on depressive symptoms and their severity. Scoring ranges from 0 to 63 (0 to 13 indicates no or very few depressive symptoms, 14 to 19 mild depression, 20 to 28 moderate depression, and 29 to 63 severe depression). The BDI-II has good reliability and validity and has shown high internal consistency [25].

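### The stated inputs (5.8 BDI-II points, SDs 4.8 and 7.8, one-sided test, 80% power) do not give 41 or 50 per group; 5.8 may be a post-measurement mean, but the document does not settle it

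*Protocol article*

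**What the plan says.** The Statistical analysis section of the protocol article bases the sample size on the change in BDI-II seen in a previous study. It states that 50 per group "was calculated as the minimum required to detect a 5.8 point decrease in BDI-II in 1) the ACT intervention group" or in the rehabilitation group, "vs. no change in 3) the caregiver support group at the 10-month post-measurement to achieve 80% power".

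On method: "The calculations were based on a one-sided General Estimation equation (GEE) model [41] using the pre-measurement, four-month and 10-month post-intervention measurements". No within-person correlation is given.

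On inputs, it assumes that the post-measurement difference between either intervention group and the support group "would be 5.8 points (*SD* = 4.8) lower than at pre-measurement (9.3 points, *SD* = 7.8").

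With 20% attrition it expects 123 participants (41 per group) and sets the target at 150 (50 per group). The following paragraph sets the significance level at 0.05 for the analyses. No separate alpha is given for the sample size.

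**The concern.** Two things look wrong.

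First, 5.8 points is large against either stated SD (5.8/7.8 = 0.74; 5.8/4.8 = 1.21). A one-sided comparison of that size should need far fewer than 41 per group for 80% power.

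Second, the sentence giving the inputs is hard to read as written. It describes a difference between groups as being lower than at pre-measurement, which mixes a between-group contrast with a within-group change. Each of 5.8 and 9.3 also carries its own SD, as pre and post means usually do.

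The clinical scale gives a further reason to look again. A mean of 9.3 already lies in the band that the Depression section describes as "0 to 13 indicates no or very few depressive symptoms". A 5.8-point fall from there is a 62% reduction (5.8/9.3), to a mean of 3.5.

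What is at stake is how the trial's sensitivity is described. This is the only effect size stated for the primary outcome. If 5.8 is the planned change, the trial has considerably more power than it claims. If the planned change was 3.5, the stated power is about right but the stated detectable effect is not. The difference matters for reading a null result, particularly as Group 3 recruited 39, below 41 even before attrition.

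**Working it through.** **Inputs from the Statistical analysis section:** effect 5.8 points against no change; SDs 4.8 and 7.8; pre-measurement mean 9.3; one-sided test; 80% power; 41 per group after attrition and 50 recruited. **Assumptions:** one-sided alpha 0.05, normal approximation, equal groups. The correlation ρ is not stated, so it is varied.

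**Formulas**
- n per group = 2 (z₀.₉₅ + z₀.₈₀)² (SD/δ)² = 2 (1.645 + 0.842)² (SD/δ)² = 12.37 (SD/δ)², rounded up.
- Pooled SD = √((7.8² + 4.8²)/2) = 6.48.
- Change-score variance = 7.8² + 4.8² − 2ρ(7.8)(4.8) = 83.88 − 74.88ρ. With 7.8 at both times it is 2(7.8²)(1 − ρ) = 121.68(1 − ρ).

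**Step 1. Try to reproduce 41 with δ = 5.8, two-sample form**

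| SD | n per group | power at 41 |
|---|---|---|
| 4.8 | 12.37 × 0.685 → 9 | above 99.9% |
| 6.48 | 12.37 × 1.247 → 16 | 99.2% |
| 7.8 | 12.37 × 1.809 → 23 | 95.7% |

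For the last row, 5.8/(7.8√(2/41)) = 3.37, and 3.37 − 1.645 = 1.72, which gives 95.7%. Neither 41 nor 50 is reproduced.

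**Step 2. Change score with both stated SDs, δ = 5.8**
- ρ = 0: 12.37 × 83.88/33.64 → 31 per group; power at 41 is 88.9%.
- ρ = 0.3: 23 per group; power at 41 is 95.6%.
- ρ = 0.6: 12.37 × 38.95/33.64 → 15 per group.

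The required size falls as ρ rises, so 31 is the maximum for any non-negative correlation. If instead 4.8 is the SD of the change itself, the pre-post contrast needs no correlation and n is 9.

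**Step 3. What does bring 5.8 points to about 41?**
- SD 7.8 at both times, one-sided 0.05: 45 at ρ = 0, 41 at ρ = 0.1, 36 at ρ = 0.2, 23 at ρ = 0.5. A three-point slope with SD 7.8 gives 40 at ρ = 0.1.
- A stricter alpha that the plan does not state. At one-sided 0.025 the factor 12.37 becomes 15.70: SD 7.8 at both times with ρ = 0.3 gives 39.7, and SDs 7.8 and 4.8 with ρ = 0 give 39.1. At one-sided 0.0125, SD 7.8 at both times with ρ = 0.4 gives 41.3.

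**Step 4. The alternative reading, δ = 9.3 − 5.8 = 3.5**
- Pooled SD 6.48: 12.37 × 41.94/12.25 → 43 per group. At 41, 3.5/(6.48√(2/41)) = 2.45, and 2.45 − 1.645 = 0.80, so power is 78.9%.
- Change score with SDs 7.8 and 4.8, ρ = 0.6: 12.37 × 38.95/12.25 → 40 per group.
- SD 7.8 alone gives 62; SD 4.8 alone gives 24.

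**Step 5. Attrition.** 41 × 1.2 = 49.2, so 50. Dividing instead gives 41/0.8 = 51.25, so 52. Starting from 43, the two methods give 52 and 54. The step from 41 to 50 therefore does not show which effect was used.

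**The case against.** The strongest reply is that the stated method is a three-point GEE, not a two-sample test, and that its correlation and alpha are not reported. Step 3 shows that 5.8 points can then give about 41. A reader might infer from the near match in Step 4 that the size reproduces only for 3.5 points; that is not so. The 3.5-point match is itself selective: it appears with the pooled SD or with ρ near 0.6, and not with SD 7.8 or 4.8 alone.

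The document also twice words 5.8 as a decrease, and a change can carry its own SD. Whether 5.8 is a post-measurement mean can be settled only in the previous study, which is not at hand. A published article may also reasonably leave the working correlation to a fuller document.

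Much of this stands, and it rules out saying that the target effect has been shown to be wrong. It does not restore agreement among the stated figures. At one-sided 0.05, the routes to 41 for 5.8 points set aside the stated SD of 4.8 and need a correlation near 0.1, which I would judge low for repeated scores on one questionnaire in the same person. The other routes need an alpha that the plan does not state. The finding is that the reported effect, SDs, power and size disagree; it does not rest on the missing correlation.

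**Conclusion.** As written, the set of effect, SDs, power and size is not supported by its own inputs. With the stated SDs and one-sided 0.05, 5.8 points needs 9 to 23 per group in two-sample form and at most 31 as a change score, against the stated 41 (50 recruited). Two-sample power at 41 is about 96% or more rather than 80%. This rests on applying the analysis alpha of 0.05 one-sided, on a non-negative correlation, and on using both stated SDs in the change score.

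That 9.3 and 5.8 are pre and post means, with a planned decrease of 3.5, is a plausible explanation that fits closely (43 per group; 79% power at 41). It is not established.

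Two stronger readings should be resisted. A reader might conclude that the target is overstated by about 66% (5.8/3.5 = 1.66), but that presumes the unproven reading. A reader might also conclude that a true 3.5-point effect would be judged a failure. The plan sets no 5.8-point success threshold: it uses 5.8 only for sample size, and interpretation rests on significance at 0.05 and Cohen's d.

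**What to change.** Check 5.8 (SD 4.8) against the previous study, then correct the sample-size paragraph accordingly.

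- If it is that study's post-measurement mean, restate the detectable effect as a 3.5-point between-group difference in change at 10 months.
- If it is a change, keep 5.8 and replace 80% with the power that 41 per group provides (about 96% or more in the two-sample form).
- In either case, give the SD, the one-sided alpha and the within-person correlation used in the GEE calculation. Reword the sentence so that it states one quantity: the difference between groups in change from pre-measurement.

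The cost is wording only. Pre-measurements are complete and 156 caregivers are recruited, so no new data are needed and enrolment is unaffected. The stated figure may become less favourable.

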#### Support provided by voluntary family caregiver associations

Caregivers from voluntary family caregiver associations, mostly giving peer support, formed a control group. Family caregiver associations support family caregivers by providing individual counseling, information about services, tools, and resources, such as peer support groups, events, trips and open cafés. The family caregiver controls were recruited from five voluntary caregiver associations. The research team contacted the associations via email, and, after obtaining permission, attended the family caregiver support group or other activities of the association to inform members about the study, and to recruit participants. The family caregivers who gave their informed consent to participate in the study, filled in the measurement package. In addition, a short physical performance test (SPPB) was performed at pre-measurement. Recruitment was implemented from March to December 2017. The mid-measurement package was sent to the caregivers at four months and the post-measurements will be carried out at 10 months after the pre-measurements. A total of 39 family caregivers were recruited from voluntary caregiver associations.

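### The sample-size statement is wrong as written: it disagrees with its own attrition rate, its own effect size and SDs, and the 39 caregivers enrolled in Group 3

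*Protocol article*

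**What the plan says.** All of the sample-size reasoning is in the protocol article, Statistical analysis. Fifty per group is described as "the minimum required to detect a 5.8 point decrease in BDI-II" in Group 1 or Group 2, against no change in Group 3, "at the 10-month post-measurement to achieve 80% power". On the method: "The calculations were based on a one-sided General Estimation equation (GEE) model", using all three measurements. The next sentence attaches an SD of 4.8 to the 5.8 points and describes the result as "lower than at pre-measurement (9.3 points", SD 7.8). Then come the attrition line, "Thus, assuming an attrition rate of 20%, a sample size of 123 (41 per group) was expected", and the target: "Hence the target sample size was 150 participants, with 50 in each group".

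For the analysis, the same section names multiple-group modelling of all participants, with full information maximum likelihood (FIML) under missing at random. On the test it says only: "The level of significance will be set at 0.05".

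The Interventions sections report final recruitment of 65 (Group 1), 52 (Group 2) and, for Group 3: "A total of 39 family caregivers were recruited from voluntary caregiver associations". Group 3 recruitment ran from March to December 2017, and the Study design section puts all pre-measurements in 2017, so these numbers are final.

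**The concern.** The paragraph supports one claim: that the trial has 80% power for each active group against Group 3. Four parts of it do not fit together.

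- The attrition arithmetic does not give 41.
- Group 3, shared by both powered contrasts, is below the stated minimum of 50 and also below the 41 expected after dropout. The total of 156 exceeds 150 only because Group 1 over-recruited.
- Power is one-sided, while the planned test has no stated direction.
- The effect and SDs quoted do not lead to the sample size quoted.

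The aims predict that the web programme is superior to association support. If that comparison is null, readers will judge it against an 80% figure that was not recalculated for the groups actually enrolled and cannot be reconstructed from the text.

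**Working it through.** **Inputs from the article:** effect 5.8 BDI-II points; SDs 4.8 and 7.8; pre-measurement mean 9.3; power 80%, one-sided; attrition 20%; target 50 per group; enrolled 65, 52 and 39.

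**Assumptions of this check:** alpha is 0.05 for the power calculation too. The working correlation of the GEE is not given, so a two-sample t-test at 10 months stands in for it.

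**1. Attrition.** 50 × 0.80 = 40 per group, 120 in total. Keeping 41 needs 41 / 0.80 = 51.25, so 52 per group. The pair 50 and 41 implies 9/50 = 18% loss. It would also arise from 41 × 1.2 = 49.2, rounded up to 50, a common inflation error. Going from 41 to 40 per group costs about one point of power (80.0% to 79.1%, or 78.3% to 77.4%, on the two assumptions in step 4).

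**2. Enrolled groups at 20% loss.** 65 × 0.8 = 52; 52 × 0.8 = 41.6, about 42; 39 × 0.8 = 31.2, about 31. FIML keeps partial data, so the effective Group 3 size lies between 31 and 39.

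**3. Does the stated size follow from the stated inputs?** Per group, n ≈ 2 (1.645 + 0.842)² (SD/δ)² = 12.37 (SD/δ)² one-sided. The t-test adds about one.

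| δ | SD | n, normal | n, t-test |
|---|---|---|---|
| 5.8 | 4.8 | 9 | 10 |
| 5.8 | 6.48 | 16 | 17 |
| 5.8 | 7.8 | 23 | 24 |
| 3.5 | 6.48 | 43 | 44 |

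Here 6.48 = √((4.8² + 7.8²)/2). The first three rows take the text literally, and none is near 41 or 50. The last row assumes that 5.8 is the post-measurement mean, so δ = 9.3 − 5.8 = 3.5. It comes close to 41 but contradicts the stated 5.8-point decrease. Another variant uses a change-score SD with zero pre–post correlation, √(7.8² + 4.8²) = 9.16. With δ = 5.8 it needs 32 one-sided; it reaches 41 only two-sided, against the text.

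**4. Power for the enrolled groups.** Power ≈ Φ(δ / (SD √(1/n₁ + 1/n₂)) − z), with z = 1.645 one-sided or 1.960 two-sided. Example, 52 v 31 with δ = 3.5: √(1/52 + 1/31) = 0.2269 and 3.5 / (6.476 × 0.2269) = 2.38. This gives Φ(0.74) = 77% one-sided and Φ(0.42) = 66% two-sided; the t-test gives 76% and 65%.

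Assumption A is δ = 3.5, SD 6.48. Assumption B takes 41 per group as exactly 80% one-sided at δ = 5.8, which requires an SD of about 10.5, above both stated SDs. The literal reading is δ = 5.8 with the larger stated SD, 7.8. T-test power, one-sided / two-sided:

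| Groups | A | B | Literal |
|---|---|---|---|
| 41 v 41 (as expected) | 78 / 68% | 80 / 70% | 95 / 91% |
| Group 1 v 3, 20% loss (52 v 31) | 76 / 65% | 78 / 67% | 95 / 90% |
| Group 2 v 3, 20% loss (42 v 31) | 73 / 61% | 75 / 64% | 93 / 87% |
| Group 1 v 3, no loss (65 v 39) | 84 / 75% | 86 / 77% | 98 / 95% |
| Group 2 v 3, no loss (52 v 39) | 81 / 71% | 83 / 73% | 97 / 93% |

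**The case against.** A reader might infer that the trial fails to deliver 80% power, or delivers it only one-sided. The documents do not establish either. At the literal 5.8 points and the larger stated SD, power is at least 87% two-sided even with 31 left in Group 3. The figures below 80% depend on assumptions that the article does not state: a 3.5-point effect, or an SD chosen to make 41 per group give 80%. (With 5.8 points and a zero-correlation change-score SD of 9.16, completers give 84–87% one-sided and 75–79% two-sided.) A single-time-point t-test is also not the three-measurement GEE. FIML keeps dropouts' earlier data, so 31 is the pessimistic end; with no loss, one-sided power exceeds 80% under both A and B.

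Three further defences are fair. The one-person attrition slip is trivial by itself. The split of 65/52/39 is disclosed openly, from the abstract on. Powering by GEE and analysing with another longitudinal model is not in itself an error, and naming a single confirmatory contrast would be a preference.

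All of that stands and limits what can be said about size. It does not rescue the paragraph. If the literal inputs are right, 50 per group is not the minimum. If the stated size is right, the enrolled Group 3 falls short of it.

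**Conclusion.** The point holds as an inconsistency in the stated sample size and power; it does not show that the trial is underpowered. Three things follow from the text alone: 50 less 20% is 40; Group 3 closed at 39 against a minimum of 50 and an expected 41; and the direction of the planned test is not stated, although the power is one-sided. A fourth follows by simple calculation: the literal inputs need about 10 to 24 per group one-sided, not 41 or 50.

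The effect on power can only be given as a range, on t-tests at alpha 0.05. Under either assumption that approximates 41 per group, power after 20% loss is about 76–78% one-sided and 65–67% two-sided for Group 1 v 3, and 73–75% and 61–64% for Group 2 v 3. With no loss it is 81–86% and 71–77% across the two contrasts. So on those assumptions a two-sided test stays below 80% even with complete follow-up. Under the literal 5.8 points with SD 7.8, it is 87–95% after loss. The article does not let a reader choose between these.

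**What to change.** No new enrolment is needed. In Statistical analysis:

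1. Correct the attrition line: either 50 per group leaves 40 (120 in total), or 41 per group needs 52.
2. State whether 5.8 is a change or a post-measurement mean, what the SD of 4.8 belongs to, and the working correlation used in the GEE, so that the sample size can be reproduced.
3. State whether the primary test is one- or two-sided, and give the power on the same basis.
4. Restate power, or the minimum detectable difference, for the enrolled 65/52/39, separately for Group 1 v 3 and Group 2 v 3, with and without the planned 20% loss.

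This changes wording and requires one recalculation. The only cost is that the stated power may become less favourable.

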## Discussion

### The aim of the study

This article describes a research protocol for a quasi-experimental trial investigating whether a guided web-based acceptance and commitment therapy (ACT) intervention (Group 1) or a standardized rehabilitation program provided by rehabilitation centers (Group 2) is more effective in reducing depressive symptoms and improving the well-being and quality of life of elderly family caregivers, compared to support provided by voluntary family caregiver associations (Group 3). A further aim is to investigate whether personality, psychological flexibility or other psychological variables predict, or mediate the effects of the web-based ACT intervention. User experiences and the satisfaction of family caregivers with the web-based intervention will also be examined. We expect the effect of the web-based intervention to be equal to the effect of the established comparator group (Group 2), and show more positive effects on depressive symptoms and well-being than the support provided by family caregiver associations (Group 3).

Family caregivers who provide complex chronic care play a crucial role in the long-term care of older adults worldwide. Several studies have shown, however, that while caring for a person with a long-term condition or disability may be rewarding, it may also have serious negative effects on the caregivers’ physical and mental health [43, 44]. Depression, stress and other types of psychological distress are major health concerns among family caregivers [5]. It is, therefore, of great importance to help to decrease the negative impact of caregiving on family caregivers. Low intensity interventions combined with technology enable 24/7 committed and stressed caregivers to participate when they have both the time and need to do so. However, it is important to evaluate the acceptability of technology-based interventions and their effects on psychological and physiological variables.

This study will provide knowledge on the effectiveness and acceptability of a web-based intervention aimed at decreasing depressive symptoms and increasing well-being and quality of life among caregivers aged 60 or more. We compare a web-based intervention with a standardized institutional rehabilitation and support provided by family caregiver associations. While the current institutional rehabilitation program has successfully met the caregivers’ physical needs, results show that it has not improved caregivers’ mental health [45]. If the web-based CareACT intervention improves family caregivers’ mental health and if their physical functioning is also found to be on an acceptable level for independent living, the web-based intervention should be made available to all family caregivers. If support received from family caregiver associations does not show changes comparable with those of the web- and institutional programs in reducing depressive symptoms, it may nevertheless offer a potential environment for implementation of the CareACT program which has proven effectiveness. In sum, this study will increase our understanding of the effectiveness and suitability of acceptance, mindfulness and value-based brief interventions for elderly family caregivers suffering from depressive symptoms and psychological distress.

